#### Participant feedback

Intervention feedback will be solicited from participants upon completion of the final testing session. Participants will be asked to provide written feedback via a Likert-based survey about their satisfaction with the program, exercise leaders and equipment used, their confidence that they could continue the program, and the likelihood that they would recommend the program to others. Participants will also be asked to provide formative feedback with open-ended questions related to intervention facilitators, barriers, and suggestions for future trials. This feedback combined with the other feasibility metrics, which includes patient burden information, will be integrated into the dissemination of the results via scientific publication and through the National Multiple Sclerosis Society. Through this feedback process, patients will be involved in the proposed research process, study result dissemination, and future study design.

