## Methods

### Recruitment

The study will recruit 15 pwMS-wd (i.e., a PDDS score of 3–6) from areas surrounding Berry College. Berry College is located in a highly accessible, rural area in the northwest of Georgia. We will recruit from areas between Atlanta, GA; Chattanooga, TN; and Birmingham, AL. Participants will be asked to provide their own transportation to Berry College. With regard to the sample population, this study focuses on the effects of HIIT in those with MS who are ambulatory, but report walking impairments, as this represents upwards of 75% of the MS community. Although the proposed range of participants (i.e., PDDS scores of 3–6) is wide, all participants within this range report at minimum gait impairment and at maximum are primarily wheelchair users but are able to walk 25 ft in under 2 min. Using this wide range will allow us to answer our key question, while maximizing our recruitment potential in a rural, likely underserved population. We will examine medication use, symptoms of spasticity, and depression in the study results.

Recruitment will occur through fliers provided to local and regional MS Society chapters, clinics, and doctor’s offices; flyers provided at local and regional MS Society events; advertisements on social media; email communication to the local and regional MS Society participants; and by word of mouth. This study will be described as an opportunity to participate in a study testing physiological and functional responses to exercise in persons with MS. Participants will be asked to contact the laboratory by telephone or email for further information about the study and screening for inclusion. See Fig. 1 for a diagram of participant movement from recruitment through completion of the program and Fig. 2 for the schedule of enrollment, intervention, and assessments.

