#### Process log

A process log will be maintained on a password-protected database to assess enrollment patterns and study feasibility. The log will contain the following demographic information: identification number, individuals’ name, and contact information. The log will also be used to track screening date, eligibility status, date enrolled, reason for ineligibility, reason for refused consent/participation, adherence, and source of subject (e.g., referral, advertising, advocacy, etc.). We will record adherence with the intervention via log books to be filled out at each completed or missed exercise session.

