**Management** (i.e., data management and safety reporting assessment)	1. IRB approval procedures 2. Time and accuracy in data collection, entry, and checking	1. All Institutional Review Board (IRB) approval procedures will be documented and will include communications between the University IRB and staff, and time from submission of IRB application to approval. 2. Data will be checked for completeness and errors. All time spent collecting, entering, and checking data will be recorded.	1. Details procedural and staff requirements for obtaining ethical approval, compliance, and monitoring. Highlights optimal safety procedures to be implemented. 2. Identifies staff time requirements and highlights considerations for alterations to ensure proper data management.
**Scientific** (i.e., safety, burden, and treatment effect assessment)	1. Adverse events, serious adverse events, and clinical emergencies 2. Participants’ experience, burden, and perceptions 3. Treatment effect	1. Adverse events, serious adverse events, and clinical emergencies will be reported and recorded. A safety plan will be enacted in the occurrence of an adverse event wherein participants will be asked to discontinue the HIIT exercise and cool-down (if currently exercising) and will be required to be free of symptoms for at least 48 h before returning to activity. 2. Participants’ experience, burden, and perceptions of intervention appropriateness will be assessed via a short survey at the end of the intervention. 3. Treatment effects will be determined via effect size and clinical meaningfulness calculations of any change in the efficacy outcome variables.	1. Establishes the safety and feasibility of the intervention and identifies considerations for alterations. 2. Determines the acceptability and highlight considerations for alterations. Identifying compliance will further allow correct conclusions to be drawn from the results. 3. Establishes data for power calculations and projected clinical impact.

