### Data analysis

All data will be entered, checked, and analyzed using SPSS Statistics (Chicago, IL). All data will initially be de-identified and checked for normality, outliers, errors, and missing entries. Process, resources, management, and scientific feasibility will be examined via descriptive statistics, percentage, and frequency analyses. The effect of the intervention will be determined using a repeated measures, 1-factor analysis of variance (Time) to identify significant changes over time. Multiple comparisons will be corrected using the Bonferroni correction. Disease type, medication use, symptoms of spasticity, and depression will be described and considered in the reporting of the study results. Overall effect sizes will be expressed as partial eta-squared, and small, medium, and large effects will be interpreted as values of 0.01, 0.06, and 0.14, respectively [49]. Feedback data will be reported via descriptive statistics, percentage, and frequency analysis.

We are defining clear Go/No Go Criteria for advancement to a RCT comparing RSTEP HIIT with MICE such that (1) 80% of participants (i.e., 12 participants) must complete at least 20 of the 24 prescribed sessions (i.e., 83%); this criterion is based on an expected dropout rate of ~ 15% [50]; (2) a clinically meaningful change in aerobic capacity and at least one additional outcome measure is required. Among those who successfully complete the trial (i.e., 83% of prescribed sessions), a half standard deviation improvement is necessary in aerobic fitness and at least one of the following outcomes: physical activity, walking, upper arm function, cognition, fatigue, or depression scores; this criterion is based on the universality of a half standard deviation threshold for detecting changes in health-related outcomes in chronic diseases [51, 52].

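### Acceptability, burden and barriers are surveyed only at the end of the programme, with no described route for early leavers, so the survey may overstate acceptability

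*Protocol article*

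**What the plan says.** The timing is fixed in two places. Under Participant feedback: "Intervention feedback will be solicited from participants upon completion of the final testing session". In Table 1 (Feasibility metrics, Scientific row), participants' experience, burden and "perceptions of intervention appropriateness will be assessed via a short survey at the end of the intervention". The Study testing overview puts post-intervention testing after 12 weeks of training, or about 24 sessions.

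The survey has two uses. Besides its Likert items it collects "formative feedback with open-ended questions related to intervention facilitators, barriers, and suggestions for future trials". Table 1 gives its importance to later studies as: "Determines the acceptability and highlight considerations for alterations".

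The Recruitment section plans for 15 participants, and the Data analysis section expects dropout: "this criterion is based on an expected dropout rate of ~ 15" per cent.

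The Process log section names the reasons to be tracked: "reason for ineligibility, reason for refused consent/participation, adherence, and source of subject". A reason for withdrawing after enrolment is not named. The same section has log books filled out for completed and missed sessions, and Table 1 has participant flow recorded through the intervention stage.

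**The concern.** Feasibility is the primary aim, and participant burden and feedback are among its named scientific outcomes. For a high-intensity programme in severely deconditioned people, one obvious question is whether some find it too demanding. People who stop for that reason are the least likely to attend a visit defined by the end of the programme. If they are not asked, the acceptability result describes mainly those who tolerated the training, and the barriers passed to the designers of the randomised trial may leave out the ones that caused withdrawal. The plan itself expects some people to leave.

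**Working it through.** **Inputs from the documents.** Planned N = 15 (Recruitment). Expected dropout about 15%, and the completion criterion of 12 participants with at least 20 of 24 sessions (Data analysis). Survey at the end only (Participant feedback; Table 1).

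**The plan's own figures.** 0.80 × 15 = 12 and 20/24 = 83.3%. Both agree with the text.

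**Expected number of leavers.** 0.15 × 15 = 2.25. If dropouts are independent, each with probability 0.15:
- at least one: 1 − 0.85^15 = 91.3%
- at least two: 68.1%
- more than three: 17.7%

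**Bound on the overstatement.** Let d be the number who leave and are not surveyed, s_c the proportion satisfied among completers, and s_d the proportion satisfied among leavers.
- Rate over all 15: [(15 − d) × s_c + d × s_d] / 15
- Overstatement if only completers are reported: s_c minus that rate = (d/15) × (s_c − s_d)

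The documents give neither s_c nor s_d, nor a cut-off that turns the Likert items into a satisfied/not satisfied split. The values below are assumptions that show the range, in percentage points.

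| s_c | s_d | d = 2 | d = 3 |
|---|---|---|---|
| 100% | 0% | 13.3 | 20.0 |
| 100% | 50% | 6.7 | 10.0 |
| 90% | 0% | 12.0 | 18.0 |
| 90% | 50% | 5.3 | 8.0 |
| 80% | 0% | 10.7 | 16.0 |
| any | equal to s_c | 0 | 0 |

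Two dropouts is closest to the plan's expectation. Three is 3/15 = 20%, above the expected rate; if those three are the only participants short of 20 sessions, the completion criterion can still be met.

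**What else is recorded on leavers.**
- *Process log:* reasons for ineligibility and for refusal, listed among screening and enrolment items, plus adherence. A reason for stopping is not named.
- *Log books:* completed and missed sessions. No satisfaction, burden or barrier items are described.
- *Participant flow:* shows how many left and when.
- *Midpoint testing:* may bring early discomforts to light, but no survey is described there, and someone who leaves before week 6 does not reach it.
- *Transportation:* recorded as a reason for declining during recruitment (Discussion), not for stopping later.

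None of these is described as asking a person who stops how acceptable or burdensome the programme was, or why they stopped.

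**The case against.** Several counter-arguments have force.

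**The decision rule is protected.** The first Go criterion reads "80% of participants (i.e., 12 participants) must complete at least 20 of the 24 prescribed sessions (i.e., 83" per cent). Each dropout who falls short of 20 sessions counts against advancement, and neither criterion uses the survey. Retention and attrition are separate process outcomes. A reader might infer that the trial's feasibility answer as a whole is biased in its favour; the documents do not support that. This argument stands in full.

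**Leavers are not excluded in words.** A reader might infer that dropouts can never be asked. The text does not bar someone who stopped training from final testing, and does not say whether such people are invited. This stands: what can be said is that no route is described.

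**The bias may be nil.** A reader might infer that satisfaction is certain to be overstated, for instance by setting 12 of 12 satisfied completers (100%, exact 95% lower limit 74%) against 12 of 15 overall (80%, 52% to 96%). That is the extreme case at 20% dropout, with every completer satisfied and every leaver not. People who leave because of relapse or transport may have liked the programme.

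**Other data exist.** Exertion ratings at every session, adverse events, and a database of all contact between staff and participants would say something about leavers. The Feasibility metrics text also lists barriers and participant experience under resource outcomes. This stands in part: such data could hint at a reason, but the resource row of Table 1 gives no instrument for barriers or experience, and none of these sources is described as a substitute for the survey.

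**The article is condensed.** Exit procedures may sit in the full protocol or the manual of operating procedures, neither of which is shown. This limits any claim that no exit contact exists. It does not answer the point about timing, which the article states twice.

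**Conclusion.** The point holds as a modest, inexpensive improvement to a descriptive outcome. As scheduled, the only described source of acceptability ratings, burden and barriers depends on reaching the end of the programme, in a trial that expects about 2 of 15 to leave. The survey result may therefore overstate acceptability and miss reasons for withdrawal.

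The possible overstatement is 0 to 13.3 percentage points with 2 dropouts and 0 to 20 with 3. This rests on three assumptions: leavers are not surveyed, all completers respond, and leavers are no more satisfied than completers. Leavers' actual views are unknown, so a value of zero cannot be ruled out. What is exposed is the acceptability description and the information meant to shape the randomised trial.

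**What to change.** Amend the Participant feedback section and the Scientific row of Table 1 as follows.

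- Offer the same Likert and open-ended survey, with an added question on the reason for stopping, to everyone who starts training: by email or phone at withdrawal for those who stop, and at final testing for the rest.
- Add the reason for stopping to the process log.
- Report completers and non-completers separately, giving the number who started training, the number who responded and the non-response. Do not count non-responders as dissatisfied.

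Using those who started training as the base keeps the group surveyed and the group reported the same. Enrolment occurs at consent, at the first baseline session, so a person who leaves before any training could not rate the programme.

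The cost is a few extra contacts through the email and phone channel already used for session reminders. Some of those who withdraw will probably not respond. Six participants had been enrolled by June 12, 2020, with recruitment expected to end on May 30, 2021, so on the article's dates 9 of the 15 were still to enrol.

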### Outcome assessments

#### Study testing overview

Baseline, midpoint (e.g., after 12 exercise training sessions), and post-intervention (e.g., after 24 exercise training sessions) testing will be performed at Berry College. All outcome assessors will undergo training prior to data collection to ensure that the final outcomes will be administered using standardized instructions and that the data will be collected consistently across time points. The outcome measures will be manualized and standardized. Midpoint testing will occur following 6 weeks of training. Post-intervention testing will occur following 12 weeks of training. The same specialized equipment for collecting baseline outcome measures will be used at the midpoint and post-intervention assessments. The use of a midpoint testing data point provides a temporal characterization of any outcome changes and may identify any discomforts in the initial stages of the program that might be overcome in the second half of the program. It further allows for modifications to the training stimulus based on any improvements after only 6 weeks of training. These data can ultimately inform therapists about the possible changes to expect if the intervention is successful and integrated into a clinical setting.

#### Participant characteristics

Descriptive characteristics of participants will be collected via a standard questionnaire. We will report mean (SD) for age, sex, employment status, MS disease type, and MS disease duration. Medication use could impact overall outcomes; thus, participants will complete a medication use questionnaire and data will be used as a control mechanism. Mean (SD) scores for item 7, “stiffness,” of the Multiple Sclerosis Impact Scale (MSIS) will be reported as a measure of spasticity experienced by participants [39]. The MSIS is a self-report measure comprised of 29 items with physical and psychological components. This Likert scale ranges from 1 (not at all) and 5 (extremely) and measures the impact of MS on day-to-day life in the past 2 weeks.

#### Disability status assessment

A Neurostatus-certified assessor (level C) will determine the disability status of participants through a clinically administered Expanded Disability Status Scale examination. The EDSS is a method of quantifying disability in MS and monitoring changes in the level of disability over time [40]. It is widely used in clinical trials and in the assessment of people with MS. The EDSS scale ranges from 0 to 10 in 0.5-unit increments that represent higher levels of disability.

#### Aerobic capacity assessment

Aerobic capacity will be assessed utilizing a standardized protocol for pwMS using a recumbent stepper [8]. The aerobic capacity data will serve as a manipulation check to ensure the intervention leads to significant fitness adaptations. Expired gases will be collected using a 2-way non-rebreathable valve, and oxygen consumption will be continuously measured using an open-circuit spirometry system. Participants will complete a 1-min warm-up at 15 W. The initial work rate will be set to 15 W and will be gradually increased until the participant reaches volitional fatigue. The work rate will be increased by 10 W per minute and 5 W per minute for participants who use a cane and walker, respectively; this yields an exercise test of approximately 8–12 min for these two groups who differ in disability level. HR using Polar H10 HR monitors and ratings of perceived exertion (RPE) via the Borg CR-10 RPE Scale will be recorded every minute. Participants will be asked to maintain a step rate of ~ 80 steps per minute [41]. Once the participant can no longer maintain a minimal cadence of 50 steps per minute or ends the test due to volitional fatigue, the assessment will be terminated. The highest recorded 30-s VO_2_ value will be recorded as VO_2peak_, expressed in mL/kg/min, when at least 1 of the following criteria are satisfied: (1) respiratory exchange ratio 1.10 or greater, (2) peak HR within 10 beats per minute of age-predicted maximum (i.e., 220-age), or (3) RPE 7 or greater. Peak HR, RPE, and wattage will also be recorded.

#### Walking assessments

Walking endurance will be assessed via the 6-min walk test (6MWT) [42]. Participants will be instructed to walk as far and as fast as possible for a 6-min period along a single corridor 75 ft in length with two, 180° turns. The protocol permits typical assistive device use and periods of rest within the 6-min period. The total distance traveled (ft) will be recorded. Walking speed will be measured using the timed 25-ft walk (T25FW) [8]. Participants will be instructed to walk as fast and as safely as possible along a clearly marked 25-ft long path. Using a stopwatch, one researcher will record the participant’s time (s) and another will follow alongside the participant for safety. This process will be repeated twice and scores will be averaged and converted into walking speed (ft/s).

#### Physical activity assessment

Device measurement of physical activity will occur using accelerometry via the ActiGraph GT3X+ accelerometer [43]. This model of accelerometer contains a solid state, digital accelerometer that generates an electrical signal proportional to the force acting on it along three axes. Participants will be asked to wear the accelerometer attached to an elastic belt on their non-dominant hip for 7 consecutive days. Participants will also be asked to log their wear time during those 7 days to ensure 10 h of wear time. Using the ActiLife software, sedentary, light, and moderate-to-vigorous counts of physical activity will be generated based on disability status [43].

#### Cognitive assessments

The Brief International Cognitive Assessment in MS (BICAMS) includes the oral version of the Symbol-Digit Modalities Test (SDMT), the first 5 recall trials of the California Verbal Learning Test-2 (CVLT-2), and the first three recall trials of the Brief Visuospatial Memory Test-Revised (BVMT-R) [44]. The SDMT measures information processing speed and involves matching 9 abstract geometric symbols with single digit numbers, whose pairings are located in a key. The task asks participants to voice correct numbers for unpaired symbols as quickly as possible for 90 s. The examiner will record responses, and the primary outcome of the SDMT will be reported as the number of correct responses provided in 90 s. The CVLT-2 measures verbal learning and memory. In this task, the examiner will read a list of 16 words, with 4 items belonging to 4 categories (e.g., vegetables, animals, furniture, and modes of transportation) that are randomly organized. The list will be read aloud 5 times in the same order, with each word voiced at a rate of approximately one word per second. Participants will be instructed to recall as many items as possible, in any order, following each reading of the list. The primary outcome of the CVLT-2 will be the total number of correct words identified over the 5 trials, with a maximum score of 90. The BVMT-R includes 3 trials of the examiner presenting a 2 × 3 array of abstract geometric figures in front of the participant. After 10 s, the array will be removed and the participants will be asked to draw the array as precisely as possible, with the figures in the correct location. Each drawing is scored on a 0 to 2 scale, based on figure accuracy and location. The primary outcome of the BVMT-R is the total raw score across the 3 trials with a maximum score of 36. Alternate forms of each of the cognitive tests will be used at each of the three time points.

#### Arm function assessment

The 9-hole peg test (9-HPT) will be used to assess upper arm function [45]. Participants are instructed to pick up pegs and place them one at a time into one of nine holes as fast as possible and then to remove the pegs, one at a time, with the same hand. The time (s) to complete this activity will be recorded and averaged on two trials for the dominant hand and then the non-dominant hand.

#### Fatigue assessment

Fatigue will be measured using the Fatigue Severity Scale (FSS) [46]. The FSS is a self-report measure comprised of 9 items that assess the severity of fatigue symptoms. This Likert scale ranges from 1 (strongly disagree) to 7 (strongly agree) and measures the degree of fatigue severity over the past week. All items will be summed for a final score with higher scores indicating greater fatigue severity and a maximum score of 63.

